## Methods and design

### Overview

We are conducting a multicentre parallel placebo-controlled randomised double-blind clinical trial with 1:1 allocation ratio. The trial is investigator initiated and controlled and good clinical practice (GCP) monitored.

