### Number of participants

Approximately 1% of parturients receive blood transfusion [7,9,32,41-44] and 1.75% develop PPH (blood loss >1000 ml) [4]. No studies conducted in the obstetric target population were available during the design phase of this trial, however, the two available RCTs found a respectively 60% [25] and 20% but insignificant [26] risk reduction in the need for allogenic blood transfusions. Thus, we settled to investigate a risk reduction of 33%: with α = 0.05 and power (β) = 80%, a number of 107 patients in each group are needed in order to evaluate a 33% reduction in the need for blood transfusion. With a margin for missing data and dropouts of 15% - a total of 245 patients will be included.

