### Statistical methods and data analysis

The two groups will be compared using chi-square test (binominal data) or Fischer’s exact test if numbers of expected values are less than five (or an unconditional exact test). Fibrinogen concentrate can potentially reverse the impaired haemostasis observed when using colloids [25,45]. The potential effect of fibrinogen concentrate may rely on the pre-administered use of colloids, so sensitivity analysis and the influence of this will be assessed together with other possible confounders (baseline variables/parameters are presented in Table 1). In accordance with ICH GCP recommendations on statistical principles for clinical trials (E9) [46], we will present adjusted and unadjusted analyses of the possible effect. The baseline variables/parameters will be assessed using multiple logistic regression models. The evaluation of pre-specified subgroups demands more participants than planned in this trial, however, to explore and guide further trials in this area we will perform two subgroups analysis: one on mode of delivery (vaginal versus caesarean section) and one on parturients with hypofibrinogenaemia at intervention, thus guiding upcoming trials in their selection of study population. All outcomes will be reported as ‘intention-to-treat’ analysis including all randomised patients fulfilling inclusion criteria and not meeting exclusion criteria with a standing consent to participate. Patients with the following major protocol violations will not be included in a supplemental per-protocol analysis: not receiving total dose and lack of follow-up. The impact of blinding level will be explored in a separate sensitivity analysis. Statistics will be performed before the code of allocation is revealed. If the overall level of missing data is less than 5%, we will perform complete case analysis. If more than 5% of missing data is the case, we will present ‘worst-case’ and ‘best-case’ analyses and if those are inconclusive, we will perform multiple imputations [47].

**Table 1 T1:** List of baseline parameters/variables to be assessed for baseline imbalance between treatment groups in the final analysis

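### The 5% missing-data rule does not say what it counts, gives no workable rule for missing covariates in the adjusted analysis, and above 5% lets the results decide whether multiple imputation is done

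*Protocol article*

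**What the plan says.** The rule is in the protocol article, under Statistical methods and data analysis. Its first branch reads: "If the overall level of missing data is less than 5%, we will perform complete case analysis". Above 5%, worst-case and best-case analyses are to be presented, and then "if those are inconclusive, we will perform multiple imputations". Neither *overall* nor *inconclusive* is defined, and no other missing-data rule is given.

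The same section promises adjusted as well as unadjusted analyses, with the baseline variables assessed in multiple logistic regression models. Table 1 lists those variables: 16 entries by my count. They include Clauss fibrinogen, TEG measures, haemoglobin, fluid volumes, estimated blood loss and two time intervals.

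Two other places bear on the point. Number of participants states: "With a margin for missing data and dropouts of 15% - a total of 245 patients will be included". Monitoring and data collection says that transfusion data come from several sources, including the regional blood bank system, and that follow-up will therefore be almost complete apart from patients who withdraw consent.

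**The concern.** There are three difficulties.

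- **The trigger may not measure the loss.** *Overall* could mean the share of data cells, the average over variables, the outcome alone, or the share of patients with any gap. Only the last of these equals what a complete-case regression discards. With the unit open, the reading can be chosen once the pattern of missing data is known.
- **Missing covariates have no workable rule.** Worst-case and best-case imputation assigns outcomes. It has no stated meaning for a missing colloid volume or TEG value, so above 5% the rule does not say what happens to the adjusted model.
- **The route above 5% depends on results.** Multiple imputation is done only if the extreme-case comparisons come out a certain way, so the set of reported analyses depends on the between-group result.

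At stake is the loss of randomised patients with a known outcome from the adjusted analysis, with lower precision and possible bias, and an unclear method for the secondary outcomes that no registry covers.

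**Working it through.** **1. The plan's own figure.** The article gives a two-group design with "1:1 allocation ratio", α = 0.05, 80% power, a 33% relative reduction and 107 per group. It does not state the control rate outright. I infer it from the two rates under Number of participants: 1% / 1.75% = 57.1%. A one-third reduction gives 38.1%, a difference of 0.1905 and a mean of 0.476. With the two-sided normal formula without continuity correction:

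n = [1.960·√(2·0.476·0.524) + 0.842·√(0.571·0.429 + 0.381·0.619)]² / 0.1905² = 106.7, rounded up to **107**, as stated.

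The total of 245 is close to 214 × 1.15 = 246.1. It gives about 122 per arm.

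**2. Loss from a complete-case adjusted model.** If k separate sources are each missing in a share m of patients, independently, the share of patients lost is 1 − (1 − m)^k. Both m and the k that applies are assumptions, because the article gives no missing rates and does not say which variables enter together.

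| Assumption | Share lost |
|---|---|
| *Overall* = share of patients with any missing value | under 5% |
| 5 covariates, 4.9% each | 22.2% |
| 6 or 7 sources, 3% each | 1 − 0.97⁶ = 16.7%; 1 − 0.97⁷ = 19.2% |
| 9 covariates, 4.9% each | 36.4% |
| 16 entries, 1% each | 14.9% |
| 16 entries, 2% each | 27.6% |
| 16 entries, 3% each | 1 − 0.97¹⁶ = 38.6% (150 of 245 left) |
| 16 entries, 4% each | 48.0% |
| 16 entries, 4.9% each | 55.2% (110 of 245 left) |

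From the second row on, every case has an average below 5% per variable, so a cell-average reading would prescribe complete-case analysis. Independence matters. If all gaps fall on the same patients, the loss at 4.9% stays at 4.9%. If gaps never overlap, it is 16 × 4.9% = 78%.

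**3. What a large loss would cost.** This is an indication only, from the simple two-proportion power formula at a risk ratio of 0.67. Power is about 84% with 122 per arm and about 67% with 81 per arm (a loss of roughly one third).

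**4. The switch above 5%.** Take 122 per arm, the design rates among patients observed, and equal missing shares m. Setting missing values to event in one arm and non-event in the other gives a difference of −0.1905·(1 − m) ∓ m.

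- 7 missing per arm (m = 0.057): −0.180 − 0.057 = −23.7 points (z = −3.7), and −0.180 + 0.057 = −12.2 points (z = −1.9).
- 18 missing per arm (m = 0.148, about the 15% allowance): −31.0 and −1.5 points.

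Just above the threshold, with the full planned effect present, one extreme passes 1.96 and the other narrowly misses it. Whether that counts as inconclusive is left open. These figures use the transfusion rates because they are the only ones that can be derived from the article. They illustrate how the rule behaves and do not forecast missing transfusion data.

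**The case against.** A reader might infer that the adjusted analysis will lose more than a third of patients. The article does not support that. It requires a cell or variable average as the meaning of *overall*, all 16 entries in one model, and largely independent gaps of about 2.5% or more each. The article speaks of models in the plural, and Table 1 is captioned as a list for assessing baseline imbalance. Many entries should rarely be missing: mode of delivery, intended procedure and blood loss are eligibility data, weight is screened, and transfused units are in the registry. Fibrinogen, TEG and haemoglobin come from the same pre-intervention sampling, so their gaps would cluster. This objection stands, and it is why the loss is given as a range.

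A reader might also infer that the primary result is in doubt. It is not, to any material degree. Transfusion is captured by registry, patients without standing consent leave the analysis set, and the unadjusted chi-square test drops nobody for a missing covariate. Nor do the extreme cases in step 4 contradict each other in direction, since both favour fibrinogen even at the 15% allowance.

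It can further be said that the sequence is pre-specified, that the extreme cases are presented and not hidden, that analysis precedes disclosure of the allocation code, and that if the extremes usually disagree, multiple imputation will usually be done anyway. These points limit the harm. They do not remove the switch, because it still turns on a comparison between the two groups, coded or not, and on an undefined term.

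Finally, an article may leave detail to the full protocol or SAP. Here, however, it fixes a threshold and a sequence in words, and those words are what is at issue.

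**Conclusion.** The point holds as a defect in the stated rule. The 5% trigger has no defined unit, missing covariates have no usable rule, and above 5% multiple imputation is conditional on results.

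The loss from the adjusted analysis cannot be fixed from the article. Depending on the meaning of *overall*, the number of covariates in the model and how far the gaps overlap, it runs from under 5%, through 17–19% (six or seven independent sources at 3%) and 39% (16 entries at 3%), to about 55% (16 entries at 4.9%). The last figure assumes independence and is not a ceiling.

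The exposure is confined to the adjusted analysis and to secondary outcomes outside the registry, such as estimated blood loss. Complete-case analysis of an outcome with under 5% missing is a common rule. To demand multiple imputation at every level of missingness would be a preference, and the finding does not rest on it. I class the point as a cheap improvement.

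**What to change.** - Apply the 5% threshold separately to each analysis, and define it as the share of patients that analysis would lose.
- Do not drop a patient from the adjusted model for a missing baseline covariate. Impute it simply and blind to arm, for example with a value taken from both arms combined. Code post-vaginal procedure as not applicable after caesarean section, so that it does not count as missing.
- Where more than 5% of an outcome is missing, name multiple imputation in advance as the method.
- Report worst-case and best-case analyses as sensitivity analyses only, and delete the condition that they be inconclusive before imputation is done.

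The cost is a few sentences in the analysis plan and a little programming. Sample size and trial conduct do not change.

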**Baseline parameter/variable**	
The level of fibrinogen before intervention defined by Clauss method (g/L)	
Presence of hypofibrinogenaemia before intervention defined by Clauss method (<2 g/L) and equivalent functional fibrinogen (TEG) MA (< 14 mm or according to validation in this study).	
Hypocoagulability prior to intervention measured with standard TEG: R-time >8 min or alpha angle <55° or MA <50 mm or LY30 >8 %	
Crystalloids used prior to intervention (ml)	
Colloids used prior to intervention (ml)	
The use of tranexamic acid prior to intervention (yes/no)	
Mode of delivery	Caesarean section
	Vaginal delivery
Post vaginal procedure	Intended manual removal of placenta
	Manual exploration of the uterus due to continuous bleeding after the birth of placenta
Estimated blood loss before intervention (ml)*	
Primary cause of PPH:	
**TRAUMA of the birth canal:** paravaginal haematoma, cervical laceration, vaginal laceration, perineal laceration, uterine rupture	
**Retained TISSUE:** Retained placental tissue, Percrete or accrete placenta	
**Impaired THROMBOSIS:** disseminated intravascular coagulation, placental abruption, severe pre-eclampsia	
**Reduced TONE of uterus:** uterine atony	
Weight of parturient (kg) (because dose of fibrinogen = 2 g/BW kg)	
Units of allogenic blood transfusion transfused prior to intervention (numbers of units)	
Bleeding duration (from start of bleeding to intervention) (min.)	
Time from birth to intervention (min.)	
Baseline haemoglobin (measured before intervention) (mmol/L or g/dL)	
Method of anaesthesia: general versus regional anaesthesia	

Adjusted analysis will be provided and results may guide further research in this field.

### Consent and ethical considerations

Patients will provide informed consent during the pre-anaesthetic assessment. An information brochure is given beforehand to all pregnant women in the Capital Region by midwives at a visit when 29 weeks pregnant, and again to women requiring labour epidural. Before the caesarean section or the post vaginal procedures patients are asked to give their informed consent. Danish law does not provide the option of including incapacitated patients using personal or professional representatives in drug trials if some of the eligible patients are able to give informed consent. The trial is approved by the National Committee on Biomedical Research Ethics 1002168/H-3-2010-004, the Danish Medicines Agency (2612–4233/EudraCT 2009-017736-41) and the Danish Data Protection Agency (2007-58-0015-00911). The trial is registered at clincialtrials.gov (NCT01359878).

## Discussion

This is the first randomised clinical trial investigating the use of fibrinogen concentrate in acutely bleeding patients in an obstetric setting. Furthermore, no previous report has evaluated the initial use of fibrinogen concentrate during acute bleeding and its possible potential effect to reduce the need for blood transfusion. In this trial, we chose to give the same pre-emptive dose of fibrinogen to all participant allocated to the intervention group regardless of body weight and plasma level of fibrinogen in order to secure treatment being given as early as possible. This implies the risk of giving a very low dose to women with high body weight and thereby potentially risking no treatment effect. On the other hand, PPH may be caused by many other factors than impaired haemostasis, such as atony or trauma of the uterus or retained tissue [48]. Once these causes have been treated bleeding usually stops. Thus by giving the same dose to all without prior measurements of the fibrinogen level, we risk giving excess fibrinogen to some. In this trial, close haemostatic monitoring with standard laboratory tests and thrombelastography including functional fibrinogen assay will reveal the haemostatic starting point and monitor any hypercoagulability that might occur.

Up to 1.9% of women giving birth in Denmark receive at least one unit of RBC postpartum [49]. Acquired hypofibrinogenaemia is a well-established cause of bleeding due to impaired haemostasis, but in most countries fibrinogen concentrate is currently approved for inherited hypofibrinogenaemia only. However, a general perception of benefits and potentials of early pre-emptive fibrinogen substitution has led to increased off-label use [34].

The substitution of fibrinogen in patients with acquired hypofibrinogenaemia is well-established as is the essential role of fibrinogen in the achievement of haemostasis in bleeding patients. However, the source of fibrinogen (FFP, Cryo versus fibrinogen concentrate) is still being debated together with the possible benefits and risks of pre-emptive fibrinogen substitution [10,24,50-54]: increasing the fibrinogen level to above normal levels in obstetric patients with bleeding might backfire, since these patients all ready have an increased risk of thrombosis post-bleeding or post-surgery [54]. Several recent reviews address the topic, but the evidence remains poor and inconclusive [10,51-53].

The FIB-PPH trial includes patients with postpartum haemorrhage. Mortality is the ultimate outcome summarising benefits and harms. However, a trial investigating this outcome in an obstetric setting would require an extremely large sample size. An ongoing randomised trial aiming at 15,000 participants worldwide investigates the use of tranexamic acid in postpartum haemorrhage with peripartum hysterectomy as outcome [55]. Trials of this scale require good organisation and funding. Therefore, with the sample size of 245 the FIB-PPH trial should be considered a pilot study, but has the benefit of being an independent investigator-initiated trial.

PPH is a potentially life-threatening acute condition and, therefore, usually not suitable for trial inclusion according to Danish laws and regulations. This could lead to selection bias, as it may be difficult to include the seriously affected women who may very well be the subgroup benefiting most from this intervention. By educating personnel and distributing information material early in pregnancy, we hope to enable the inclusion of the relevant population. Investigation of drugs considered for the treatment of acutely ill patients, such as those with acute bleeding remains a challenge due to the need for maintaining a balance between the patients’ rights for information and consent while at the same time trying to provide evidence-based treatment strategies. The use of personal or professional representatives giving the initial consent is considered legal and practised with success in some countries [55].

A positive result, indicating a potential transfusion sparring effect after births complicated by PPH, could have great importance for developing countries. Fibrinogen concentrate can be stored for five years at room temperature and no thawing or crossmatch is needed. A negative result may indicate that early treatment with a standard dose is potentially insufficient and further research would be needed into thrombelastography-guided treatment algorithms with a tight haemostasis control.

## Trial Status

The trial was initiated in June 2011 with a gradual start at each centre. By November 2011, all four centres were including participants. By June 25, 102 parturients had been included.

We hope to increase the inclusion rate as well as the proportion of patients with severe bleeding as the trial will be fully implemented as part of the daily routine at each hospital in the coming period.

## Abbreviations

APTT, activated partial thromboplastin time; FIB-PPH, fibrinogen as initial treatment of postpartum haemorrhage trial; FFP, fresh frozen plasma; GCP, good clinical practice; Hb, haemoglobin; ICH, International Conference on Harmonisation; INR, international normalised ratio; n, numbers of patients in trial; PPH, postpartum haemorrhage; RBC, red blood cells; RCT, randomised controlled trial; TEG, thrombelastography.
